## Potential Risks

A pharmacist-led educational protocol not only helps patients understand AR management but may also serve as a general guide for healthcare providers to learn about this disease management. This would enable healthcare providers to deliver concordant care in a standardised manner in an effort to achieve medication adherence and attain improved clinical outcomes (Meltzer et al., 2017).

The foreseeable risk to the participants is minimal. The participant who will be assigned at random to either the control or intervention group will be receiving usual care while the intervention group will be receiving a pharmacist-led educational protocol. Physically, there is no investigational product in this study, the participants will not be exposed to any new substances.

The participants will be asked for their demographic details, and they will be asked to self-administer a validated questionnaire assessing their knowledge with regards to intranasal corticosteroid, symptom control, and quality of life. Additionally, they will be given a diary card to record their medication usage. None of the tools used involved any sensitive questions or invasive procedures. The questionnaire administration process and daily recording of medication intake will not affect the participants from psychological, social, legal, or economic perspectives.

The participants will be followed up on day 60 $\pm$ 7, 120 $\pm$ 7 and 180 $\pm$ 7. They will need to allocate some time to answer the questionnaire. The follow-up could be conducted in the form of a physical visit to the clinic should they be scheduled for a doctor's appointment, or they will be followed up virtually using Zoom or Google Meet. No additional expenses will be incurred for the participants. The need for participant follow-up is important to determining the long-term sustainability of knowledge and behaviour change as reflected in the outcomes (symptom control and quality of life) after receiving a pharmacist-led education protocol versus those receiving usual care.

Shortening the duration of follow-up for the participants has been considered. However, in the consideration of the robustness of the pharmacist-led educational protocol, up to 180 days of follow-up would increase the overall effectiveness of the research effort to better convince health policymakers to adapt this protocol for clinical practice (Salkind, 2022).

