## 5 STUDY DESIGN

### Study endpoints

The primary and secondary endpoints of this study are shown in table 1

Table 1: study endpoints

| Primary endpoint                          | Descriptions                                                                                                                                                             |
|-------------------------------------------|--------------------------------------------------------------------------------------------------------------------------------------------------------------------------|
| 1. Knowledge of intranasal corticosteroid | The mean scores of participants who correctly answer each question in the control and intervention groups with regard to the intranasal corticosteroid.                  |
| 2. Symptom control                        | The mean difference in symptom control between the control and interventional groups.                                                                                    |
| 3. Medication adherence                   | The mean adherence rate difference for the number of doses of intranasal corticosteroid spray taken by the participant between the control and interventional groups.    |
| 4. Quality of Life                        | The mean difference in quality of life between the control and interventional groups.                                                                                    |
| Secondary endpoint                        | Within group changes from Day 0, to Day 60 $\pm$ 7, Day 120 $\pm$ 7 and Day 180 $\pm$ 7 for knowledge level, symptom control, medication adherence, and quality of life. |

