### Study design

This study will be conducted at the Hospital Raja Permaisuri Bainun in the state of Perak, Malaysia. A pharmacist-led educational protocol that has been validated by the researchers in other study will be adapted as an interventional tool for this study. This pharmacist led-protocol consists of patient education material and structured pharmacist counselling.

This trial is a single-centre, randomised, two-arm, and parallel-group controlled trial that will be conducted to determine the effectiveness of the pharmacist-led educational protocol. Adult patients diagnosed with moderate to severe AR who attend an outpatient ENT (ear, nose and throat) clinic in Hospital Raja Permaisuri Bainun will be recruited and randomly allocated at a 1:1 ratio into control and intervention groups.

The control arm will receive the current standard of pharmaceutical care, i.e., it is a health service that patient obtaining their medication from the outpatient pharmacy following a session of medical consultation at the ENT clinic, whereas the intervention arm receives the educational material and pharmacist counselling plus standard pharmaceutical care.

Baseline data will be collected and both groups will be followed up post-randomization on Day  $60 \pm 7$ , Day  $120 \pm 7$  and Day  $180 \pm 7$ . Participants will be contacted virtually (Zoom, Google Meet, or Whatapps call, or telephone call) or face-to-face, depending on the feasibility and standard operating procedures of the outpatient ENT (ear, nose, and throat) clinic at Hospital Raja Permaisuri Bainun during the follow-up on Day  $60 \pm 7$  and Day  $120 \pm 7$ . Meanwhile, the end-of-study follow up will be done at the routine scheduled clinic visit, which is around Day  $180 \pm 7$ .

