#### **Sampling technique**

A consecutive sampling method will be applied to recruit adult patients who fulfil the inclusion and exclusion criteria upon their visit to the outpatient ENT clinic. When a patient meets the enrolment criteria and agreed for participation, the designated personnel will randomize the subject. Subjects will be randomized using blocked randomization to

randomly assign the participants into control and intervention groups. An excel sheet will be used to generate a block size of 10 random numbers, 5 in each group. Each number will be kept in opaque, sealed envelopes. Consented participants will be instructed to select the sealed envelopes, and the envelopes will be opened by the researchers. The information will be recorded in the screening and enrolment log (appendix C). Subjects will be randomly assigned in a 1:1 ratio to one of two arms: (1) Intervention, or (2) Control. Measure taking to minimise bias

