### ***Measurement of symptoms control***

Total nasal symptom scores (TNSS) (Appendix F), a validated tool that enables patients to self-rate their specific nasal symptoms including nasal obstruction, itching, sneezing, secretion, runny nose, and sleep difficulty on a 4-point Likert scale ranging from 0 (no symptom) to 3 (severe symptom) in the past 12 hours and 2 weeks, is found appropriate to be adapted for symptom control assessment. The psychometric properties of TNSS is belonged to the copyright holder and thus it cannot be shared (Downie et al., 2004). The decision to select this tool is based on careful discussion with the expert opinion (rhinologists) in the consideration of the aspects of its simplicity for administration to the patients, its ability to provide objective measurement of patients' self-reported symptoms, and its potential to be used in daily clinical practice. In addition, TNSS has been widely used in randomised controlled trials and adapted in many countries. It is the most accepted primary efficacy variable that is rated for drug approval in AR by the U.S. Food & Drug Administration (U.S. Food and Drug Administration, 2020). Permission to adapt TNSS to be used in this study has been granted. In addition, permission to translate TNSS into a Malay version has also been granted by following linguistic validation methodology where it involves forward and backward translation, review by clinicians, conduct of cognitive interviews, and proof-reading (Acquadro et al., 2012). Symptom control will be assessed at baseline, on Day 60 $\pm$ 7, Day 120 $\pm$ 7, and Day 180 $\pm$ 7.

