| Four structured questions                    | The choice of responses is either yes, not sure, or no                                                                                                                                                                                                                                                                                                                                                       | Categorical |
| Total Nasal Symptom Score (TNSS)      |                                                                                                                                                                                                                                                                                                                                                                                                              |             |
| Total Nasal Symptom Score                    | The sum of the scores of the four nasal symptoms self-rated by the patients will be presented as mean and standard deviation                                                                                                                                                                                                                                                                                 | Continuous  |
| Medication adherence                  | The mean adherence rate will be calculated by dividing the number of doses administered with intranasal steroid spray by the total number of doses the intranasal steroid spray is prescribed for. The rate will be presented in mean scores and standard deviation                                                                                                                                          | Continuous  |
| EQ-5D-5L                              |                                                                                                                                                                                                                                                                                                                                                                                                              |             |

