| Timepoint          | Screening,
D0 | Baseline,
D0 | D60 $\pm$ 7 | D120 $\pm$ 7 | D180 $\pm$ 7 |
|--------------------|------------------|-----------------|-------------|--------------|--------------|
| ENROLLMENT: |                  |                 |             |              |              |
| Eligibility screen | x                |                 |             |              |              |

|                                                      |  |   |   |   |   |
|------------------------------------------------------|--|---|---|---|---|
| Informed consent                                     |  | x |   |   |   |
| Randomization                                        |  | x |   |   |   |
| Demography & medical history                         |  | x |   |   |   |
| INTERVENTION:                                 |  |   |   |   |   |
| Educational materials                                |  | x |   |   |   |
| Pharmacist counselling                               |  | x | x | x | x |
| ASSESSMENT:                                   |  |   |   |   |   |
| Disease severity classification using ARIA guideline |  | x | x | x | x |
| Endoscopy assessment                                 |  | x |   |   | x |
| Knowledge level                                      |  | x |   | x | x |
| Symptoms control                                     |  | x | x | x | x |
| Medication adherence*                                |  |   | x | x | x |
| Quality of life                                      |  | x | x | x | x |
| Concomitant medication                               |  | x | x | x | x |

\* Patients will fill-up diary card throughout the study period on medication they have taken

Participants' knowledge levels will be evaluated by self-completing a questionnaire assessing their knowledge (appendix E). Their knowledge level will be evaluated at Day 0 (baseline), Day 120±7, and Day 180±7 during their clinic visit.

Participants' symptom control will be assessed by the researcher using TNSS (appendix F). They will be asked to reflect on their symptoms in the past 12 hours and the past 2 weeks. Symptom control will be monitored at Day 0 (baseline), Day 60 ±7, Day 120±7 and Day 180±7.

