Participants' medication adherence levels will be evaluated by asking the subject to record the diary card with details on the prescribed intranasal corticosteroid during the study (appendix G). A nasal spray administration diary card will be given to the participants on Day 0. Their adherence will be assessed during Day 60 ±7, Day 120±7 and Day 180±7. If virtual follow-up is conducted on Day 60±7 and Day 120±7, participants will be asked to take a photo of their diary card and send it to the researchers, while those without a smart phone device will be required to bring along the diary card at the end of follow-up. A phone call will

be made prior to the scheduled visit (Day 180  $\pm$ 7) to remind them to bring along the diary card. If the participants have a scheduled visit at the clinic, they will be asked to bring along the diary card.

The participants' QoL will be evaluated by self-completing EQ-5D-5L (appendix H). Their QoL will be monitored at Day 0 (baseline), Day 60 $\pm$ 7, Day 120 $\pm$ 7 and Day 180 $\pm$ 7. Two sets of paper EQ-5D-5L will be given to participants without a smart phone for them to self-complete at home during virtual follow-up on Day 60 $\pm$ 7 and Day 120 $\pm$ 7, and they are required to bring them along to the clinic (Day 180 $\pm$ 7). Participants with a smart phone will be asked to complete the questionnaire electronically (Google Form) during virtual follow-up on Day 60 $\pm$ 7 and Day 120 $\pm$ 7. If their follow-up appointment is at the same time as a scheduled clinic visit, they can complete the questionnaire on paper or online (using a Google form).

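### TNSS, a primary endpoint, is self-rated in most of the plan but researcher-assessed in the data-collection text, with no self-completion route stated for virtual visits

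*Combined protocol and SAP*

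**What the plan says.** Symptom control is one of four primary endpoints, defined in Table 1 as "The mean difference in symptom control between the control and interventional groups" and measured by TNSS at Days 0, 60, 120 and 180.

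The plan describes how TNSS is obtained in two ways.

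- **Self-rated.** Potential Risks says of participants that "they will be asked to self-administer a validated questionnaire assessing their knowledge with regards to intranasal corticosteroid, symptom control, and quality of life". Measurement of symptoms control calls TNSS "a validated tool that enables patients to self-rate their specific nasal symptoms". Table 2 defines the variable as "The sum of the scores of the four nasal symptoms self-rated by the patients". Appendix F is a form addressed to the patient, in English and Malay.
- **Researcher-assessed.** The Data collection text after Table 3 says that "symptom control will be assessed by the researcher using TNSS (appendix F"). The paragraph just before it has knowledge self-completed, and the text shortly after says "QoL will be evaluated by self-completing EQ-5D-5L (appendix H").

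Days 60 and 120 may be virtual: "Participants will be contacted virtually (Zoom, Google Meet, or Whatapps call, or telephone call) or face-to-face". For those contacts the plan gives EQ-5D-5L a Google Form, or take-home paper for people without a smartphone, and has the adherence diary photographed and sent in. It gives no route for TNSS.

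On allocation, Sampling technique says "the envelopes will be opened by the researchers". The Appendix D visit form has an Intervention/Control box. No blinding of participants, researchers or assessors is described. Table 3 schedules counselling at every visit at which TNSS is taken, with no stated order.

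**The concern.** Site staff could follow either description. If they follow the Data collection text, a primary endpoint made of four 0–3 ratings is obtained through someone who probably knows the arm. Prompting, or settling a hesitant answer between adjacent categories, could then differ between arms. A P value cannot separate such a shift from a treatment effect.

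The exposure is larger for TNSS than for the other questionnaires for two reasons. Knowledge and EQ-5D-5L are expressly self-completed. And the trial has 70 per arm, set by EQ-5D-5L utility, where the plan's own TNSS calculation asks for 18 per arm, so small systematic TNSS differences reach significance easily.

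**Working it through.** **Inputs** (Sample size section): TNSS means 3.991 and 5.704, SDs 2.2145 (n = 181) and 2.2341 (n = 182), 4 measurements, correlation ρ = 0.5, α = 0.05, 70 evaluable per arm. The size of any interviewer shift is not in the documents; it is an assumption, shown as a range.

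**1. Reproduce the plan's TNSS figure.**
- Pooled SD = √[(180 × 2.2145² + 181 × 2.2341²)/361] = 2.2243.
- f = (1.713/2)/2.2243 = 0.3851.
- λ = f² × N × m/(1 + (m − 1)ρ) = 0.385055² × 36 × 4/2.5 = 8.540.
- Critical F(1, 34) = 4.130; power = 0.8103.

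These match the plan's N = 36, λ = 8.5402 and power 0.8103.

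**2. Precision of the group test with 70 per arm.** The between-group test compares four-visit means.
- SE = 2.2243 × √[(1 + 3 × 0.5)/4] × √(2/70) = 0.297.
- t(0.975, 138 df) = 1.977, so an observed difference of 1.977 × 0.297 = 0.59 point gives P = 0.05.
- A shift b at the three follow-ups only moves the four-visit mean by 0.75b, so the matching shift is 0.59/0.75 = 0.78 point at each follow-up.
- For ρ from 0.3 to 0.7 (assumed range) that becomes 0.68 to 0.87 point.

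**3. Chance of P<0.05 with no true effect.** λ = (k × b/SE)², referred to noncentral F(1, 138). Here k = 0.75 if the shift is at all three follow-ups and k = 0.5 if it is only at the two virtual visits. Example: b = 0.5, k = 0.75 gives λ = (0.375/0.297)² = 1.59 and 24%.

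| Assumed shift b (points, 0–12 scale) | Three follow-ups | Two virtual visits only |
|---|---|---|
| 0.25 | 10% | 7% |
| 0.5 | 24% | 13% |
| 0.75 | 47% | 24% |
| 1.0 | 71% | 39% |

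**4. Group-by-time test.** The SAP text does not say which term of the two-way ANOVA decides the result, so the interaction was checked too. With δ the shift at each of the four visits, λ = (70/2) × Σ(δ − mean δ)²/[SD² × (1 − ρ)] on 3 and 414 df. A shift at the three follow-ups gives 24%, 51% and 78% for 0.5, 0.75 and 1.0 point. A shift at the two virtual visits only gives 32%, 65% and 90%.

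**5. Scale.** 0.59/1.713 = 34% of the planned difference; 0.78/1.713 = 46%; 0.59/12 = 5% of the scale range.

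**The case against.** The best reply is that this is loose wording. Three sections and the form itself favour self-rating. The sentence after the disputed one has participants reflecting on their own symptoms, which fits a researcher handing over or reading out a form that the patient rates. That is a fair reading. But the plan uses self-completion wording for the measures on either side, so the disputed sentence can be followed literally, and the missing virtual route remains whichever reading is right.

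Four stronger readings are tempting, and the documents do not support them.

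- *TNSS at virtual visits can only be asked aloud.* The plan is silent on the route; it does not exclude self-completion.
- *The collector is the pharmacist who counselled the patient.* No section says so. The investigators include pharmacists, a medical officer and ENT consultants. The group box is on the Appendix D form; the TNSS form as shown has none. Knowledge of the arm is likely, not documented.
- *A shift at every visit.* The same shift at all four visits would give 13%, 39% and 92% for 0.25, 0.5 and 1.0 point. That needs the bias to be present at baseline as well, which nothing in the plan suggests.
- *Mixing telephone, video and in-person contact biases the comparison.* The same rule applies in both arms, and nothing shows that the mix would differ between them.

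It is also fair to say that a very small shift does limited harm: 0.25 point at each follow-up raises the false-positive rate from 5% to about 10%. And participants know whether they were counselled, so self-completion does not deal with their own expectations.

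**Conclusion.** The point holds as an internal contradiction about how a primary endpoint is collected, together with a missing self-completion route at up to two of the three follow-ups. It should be corrected before recruitment.

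The plan does not show that TNSS will be biased, and a reader should not infer that any trivial interviewer effect would produce a positive result. An observed difference of about 0.59 point in the four-visit mean, or 0.78 point at each follow-up, is what reaches P<0.05. A sustained half-point shift between arms would make a false-positive group test roughly one chance in four instead of one in twenty.

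These figures rest on the plan's SD and correlation, 70 evaluable per arm, no true effect and, for the interaction test, equal correlations between visits. That the collector knows the arm is inferred from the envelope procedure and the absence of any described blinding.

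**What to change.** Reconcile the sections by rewriting the Data collection sentence along these lines: in both arms, the participant completes TNSS personally at Days 0, 60, 120 and 180, before any counselling at that visit, on paper in clinic or, at virtual contacts, by the Google Form or take-home paper route already used for EQ-5D-5L. Where self-completion is impossible, the items are read out verbatim and the mode is recorded. Add a sensitivity analysis that excludes read-out scores.

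The cost is one protocol sentence, one line in the analysis section, and four items (each with its two recall periods) added to an existing electronic form. A few participants without a smartphone will still need paper or read-out. The change removes interviewer influence; it leaves the expectation bias of participants who know their arm, and the report should say so.

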### Inclusion

1. Malaysian, aged 18 to 80, with medical diagnoses of moderate to severe allergic rhinitis graded according to ARIA guidelines, who attended an ENT outpatient clinic in the period of study, and
2. capable of reading and writing in English or Malay

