| Smoking status                               | 
 
Current smoker: <math>\geq 100</math> cigarettes and still smoked daily or quit within 1 year of admission
 
Former smoker is defined as a former smoker smoked <math>\geq 100</math> cigarettes and quit more than 1 year.
 
Never smoke: an adult who has never smoked, or who has smoked less than 100 cigarettes in his or her lifetime.
 
 | Categorical |
| Comorbidity                                  | Comorbidities other than asthma                                                                                                                                                                                                                                                                                                                                                                              | Categorical |
| Asthma                                       | The control of asthma for patients who have concurrent asthma.                                                                                                                                                                                                                                                                                                                                               | Categorical |
| Frequency of AR graded according to ARIA     | Intermittent or persistent AR symptoms                                                                                                                                                                                                                                                                                                                                                                       | Categorical |
| Severity of AR graded according to ARIA      | Mild or moderate/severe AR                                                                                                                                                                                                                                                                                                                                                                                   | Categorical |

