The participants will be asked for their demographic information (date of birth, gender, occupation, ethnicity, and smoking status) and this will be recorded at enrolment. In order to characterise smoking status, the definitions of "current," "former," and "never smoker" were adopted (Centers for Disease Control and Prevention, 2017). Subsequently, participants will be assessed for their medical and allergic history, and information regarding underlying diseases will be recorded at enrolment. This information will be obtained by interview or from medical records. Subjective measurement of allergic rhinitis classification will be graded according to ARIA guidelines at baseline and during follow-ups on day  $60 \pm 7$ ,  $120 \pm 7$  and  $180 \pm 7$ . According to the ARIA guideline, the patients will be asked for their frequency of symptoms experienced, in which intermittent is defined as  $< 4$  days per week or  $< 4$  weeks at a time, while persistent is defined as  $\geq 4$  days per week and  $\geq 4$  weeks at a time. Their severity will be rated either as "mild" as defined as normal sleep, daily activities, work/school and no troublesome symptoms; or "moderate/severe" as defined as one or more of the symptoms, including abnormal sleep, impairment of daily activities, sport, leisure, problems at work or school, and troublesome symptoms. The possible allergic classifications will be intermittent mild, intermittent moderate/severe, persistent mild, or persistent moderate/severe.

Meanwhile, objective measurement of disease severity will be determined via endoscopic assessment for middle turbinate oedema grading by the physician at baseline and on Day  $180 \pm 7$ . The endoscopic assessment is one of the routine tasks that physicians perform to determine the disease progression of AR. The rationale that this assessment be performed at baseline and end of study is based on expert opinions where improvement of the middle turbinate can be seen between 4 and 6 months when patients are adhering to the intranasal corticosteroid treatment. To reduce the burden on the physicians and patients, it is deemed appropriate to schedule patients to come for a clinic visit for this assessment alongside seeking medical consultation.

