## **Statistical analysis**

An intention-to-treat analysis will be used to include all of the patients who were assigned to each group after randomization. The data analysis will be done using SPSS version 20.0. Descriptive data will be expressed as mean and standard deviation (SD) if the data is normally distributed, or median and interquartile range (IQR) if the data is not normally distributed. Categorical data will be presented in frequency and percentage.

To determine the knowledge level, The “yes” answer will be given a score of two, the “no” answer will be given a zero score, and “not sure” will be given a score of one (Retinasekharan et al., 2021). The outcome will be presented in mean score and standard deviation for each group. Each question will be analysed separately. The knowledge levels will be assessed at baseline, Day 120 $\pm$ 7 and on Day 180  $\pm$ 7. Between-group comparisons will be analysed using Two-way repeated measure ANOVA to compare mean score different between two groups. Meanwhile, the two-way repeated measures ANOVA will show the findings for the within-group comparison. A P-value of < 0.05 will be considered statistically significant.

The Total Nasal Symptom Score (TNSS) is the sum of scores for each of nasal congestion, sneezing, nasal itching, and rhinorrhoea at each time point, using a four-point scale (0–3), where 0 indicates no symptoms, a score of 1 for mild symptoms that are easily tolerated, a

score of 2 for awareness of symptoms that are bothersome but tolerable, and a score of 3 is reserved for severe symptoms that are hard to tolerate and interfere with daily activity. A higher score indicates the more severe the symptoms are, and the main outcome of TNSS will be generated as a mean and standard deviation. A mean score will be calculated separately for the past 12 hours and past 2 week. A two-way repeated measure ANOVA analysis will be employed to determine the mean difference between the scores of the control group and the interventional group in order to determine the overall effectiveness of the intervention. Within-group comparisons will be shown as part of the outcome of the two-way repeated measures ANOVA. A value of  $P < 0.05$  is considered statistically.

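### Two TNSS recall windows are tested for one primary endpoint without saying which decides; the past-2-weeks score should be named, because the 12-hour score suits intermittent disease less well

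*Combined protocol and SAP*

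**What the plan says.** Table 1 (Study endpoints) lists symptom control among four primary endpoints and defines it as "The mean difference in symptom control between the control and interventional groups". It names no recall window.

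Measurement of symptoms control adopts the TNSS with ratings "in the past 12 hours and 2 weeks, is found appropriate to be adapted for symptom control assessment". The Data collection text after Table 3 repeats both windows: "They will be asked to reflect on their symptoms in the past 12 hours and the past 2 weeks". The form in Appendix F has a column for each.

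Statistical analysis states: "A mean score will be calculated separately for the past 12 hours and past 2 week". It then compares the arms by two-way repeated-measures ANOVA at P < 0.05, "in order to determine the overall effectiveness of the intervention". It does not rank the windows and gives no multiplicity rule.

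Eligibility restricts severity but not frequency: patients enter "with medical diagnoses of moderate to severe allergic rhinitis graded according to ARIA guidelines". Table 2 records frequency as "Intermittent or persistent AR symptoms", and Data collection confirms that intermittent moderate/severe disease can occur: "The possible allergic classifications will be intermittent mild, intermittent moderate/severe, persistent mild, or persistent moderate/severe". Intermittent means under 4 days per week or under 4 weeks at a time. Follow-up is at Days 60, 120 and 180, each with 7 days' leeway either side. Nothing links these visits to symptoms.

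**The concern.** There are two linked problems.

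First, one primary endpoint yields two separately scored results, each open to a test at 0.05. If either may be claimed as success, the type I error for symptom control exceeds 5%. If the two disagree, the plan does not say which answers the primary question, and the choice would be made with the results in view.

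Second, the windows are not equally suited to the question. Potential Risks says that follow-up to Day 180 is meant to show whether the benefit lasts. A participant who is intermittent by the days-per-week rule has symptoms on at most 3 days in 7, so a 12-hour window can miss the disease altogether. A near-zero score on such a day tends to shrink the difference between arms and adds variance. The three follow-up 12-hour windows cover 36 hours of 180 days (1.5/180 = 0.8%); the three 2-week windows cover 42 days (42/180 = 23%). Coverage is not precision, but it shows how small a sample the shorter window takes.

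**Working it through.** **Two tests of one endpoint.** If the tests were independent, the familywise error would be 1 − 0.95² = 0.0975. Both windows are rated on the same form at the same visits, so positive correlation is likely and the true figure would be lower.

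**The plan's own TNSS figure** (Sample size). The means are 5.704 (control) and 3.991 (intervention), with SDs 2.2341 (n = 182) and 2.2145 (n = 181). There are 4 measurements with correlation 0.5.

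- Pooled SD = √[(180 × 2.2145² + 181 × 2.2341²)/361] = 2.2243.
- f = 1.713/(2 × 2.2243) = 0.3851.
- λ = f² × N × 4/(1 + 3 × 0.5). At N = 36, λ = 8.540, critical F = 4.130 and power = 0.8103.

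This reproduces the plan's 18 per group. At the planned 70 per group (N = 140), power exceeds 99.9%.

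**Illustrative dilution of the 12-hour score.** The documents do not give the share p of participants who are intermittent by the days rule, so a range is used. The assumptions are:

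- The plan's inputs describe symptomatic days.
- A symptom-free day scores 0.
- Intermittent participants are symptom-free on 4 days in 7, the same in both arms.
- Correlation stays at 0.5.

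The formulas are:

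- Symptom-free fraction z = p × 4/7.
- Difference = (1 − z) × planned difference.
- Arm variance = (1 − z) × SD² + z(1 − z) × mean².
- Standardised difference d = difference/√(average arm variance), and f = d/2 goes into the formula above.

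At p = 0.5, z = 0.286 and the difference is 0.714 × 1.713 = 1.224. The arm variances are 10.17 and 6.79, so the SD is 2.91, d = 0.42 and f = 0.21. At N = 140, λ = 9.89 and power is 88%.

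| Share p | d | Needed per group, planned effect | Power at 70 per group, planned effect | Power at 70 per group, half the effect |
|---|---|---|---|---|
| 0 | 0.77 | 18 | >99.9% | 82% |
| 20% | 0.58 | 31 | 99% | 56% |
| 30% | 0.52 | 38 | 97% | 46% |
| 50% | 0.42 | 57 | 88% | 32% |

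Half the effect is also an assumption. It is plausible because the sizing source compared an intervention with placebo, whereas here education is added to usual care that both arms receive.

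**A second model.** Here symptomatic and symptom-free days switch independently between visits. An intermittent participant is symptomatic at a visit with probability q = 3/7. The score variance at a visit is q(SD² + mean²) − q² × mean², the covariance between visits is q² × 0.5 × SD², and the variance between the two classes of participant is added. At 70 per group, shares of 25% and 50% give 98% and 91% power at the planned effect, and 51% and 36% at half of it. At the planned effect power is still about 80% if every participant is intermittent. If symptoms are rarer (q = 1/7), power at the planned effect is 90% and 62% for the same two shares.

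**Relaxing the equal-fraction assumption.** Suppose half the participants are intermittent, with symptoms on 3/7 of days under control and 2/7 under intervention. The difference becomes 0.714 × 5.704 − 0.643 × 3.991 = 1.51, with SD 2.92 and d = 0.52. The requirement is 38 per group instead of 57, and power at half the effect is 64% instead of 32%.

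**The case against.** The 12-hour score is never labelled primary; its equal standing follows only from the absence of a ranking. The analysis text can also be read as describing one ANOVA of the scores, not one per window. The tool was chosen after discussion with rhinologists, with both windows on the form. All of this is fair, and it leaves the gap in place: two results under one primary endpoint, and no statement of which counts.

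A reader might go further and infer that the 12-hour test is diluted to the point of being underpowered, or that its null result would count against effectiveness. The documents do not support either reading:

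- They give no share of intermittent participants, and the under-4-weeks route into that class need not mean symptom-free days every week.
- The sizing source itself mixed intermittent and persistent disease, and its recall window is not stated. Some dilution may already be in the planning figures.
- Education covers adherence and allergen avoidance and might reduce the number of symptomatic days. Zeros on the 12-hour score could then carry treatment signal, as the last calculation shows.
- At the planned effect, the 31, 38 and 57 per group in the table are all below the planned 70.
- No rule says what a null 12-hour result would mean.

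A simple two-sample calculation at half the effect gives lower power (62% undiluted, down to 22% at a 50% share), but it drops the repeated measures that the plan specifies.

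The 2-week score has limits of its own. It leans more on memory, and the whole window can lie within a remission.

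**Conclusion.** The point stands as a gap in the endpoint definition, with a good reason to close it in favour of the 2-week window. Two unadjusted tests serve one primary endpoint (9.75% familywise error under independence, less under positive correlation), and no rule covers disagreement between them. The 12-hour score is the noisier measure of sustained control in a trial that admits intermittent disease and does not time visits to symptoms.

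The loss of power is illustrative only. With 20% to 50% intermittent and equal symptom-free fractions in both arms, it is small at the planned effect and becomes serious if the true effect is about half of that. If few participants are intermittent, or if education reduces symptomatic days, the loss is smaller; if symptoms are rarer than 3 days in 7, it is larger. The change is worth making, but this is not evidence that the trial is too small.

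**What to change.** In Table 1 and in the TNSS paragraph of Statistical analysis, define primary symptom control as the between-group difference in the past-2-weeks TNSS. State that the past-12-hours TNSS is supportive and will be reported whatever it shows. One sentence in each place is enough, and it should be settled before outcome data are examined.

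Appendix F, the visit schedule and the sample size stay as they are. The price is somewhat more reliance on recall, and the 2-week score can still miss remissions longer than 2 weeks. Reporting the 12-hour score alongside it keeps that visible.
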